**Affiliations**:

1. Gynecology and Obstetrics department, University Hospital Mongi Slim La Marsa.

2. Faculty of medicine of Tunis, University Tunis El Manar.

1. **Introduction:**

Background and rationale:

Induction of labour (IOL) is a common practice in obstetrics(1). It involves the artificial initiation of uterine contractions before their spontaneous onset in order to achieve a vaginal delivery. IOL is mainly indicated in during the third trimester when there is a risk to the fetus or the mother to continue the pregnancy.

Amniotomy, also known as artificial rupture of membranes (ARM), and synthetic oxytocin (Syntocinon^®^) remain the main methods used for IOL when the cervix is favorable (Bishop score ≥ 6)(2).

There is ongoing debate about the efficacy of amniotomy in cases of IOL, some authors suggested that it has the potential to reduce the duration of labor(3–8). Nonetheless, it is important to note that amniotomy also carries an increased risk of complications, including umbilical cord prolapse, chorioamnionitis, and neonatal sepsis(9–11).

Objective: To evaluate the impact of early amniotomy on the time to active phase of labor (APL), duration of labor, as well as maternal and neonatal outcomes during IOL.

Trial design: It will be is a randomized controlled, non-blind trial. Participants will be randomly assigned to two parallel-groups: Group A: Early amniotomy (EA) and Group B: Late amniotomy (LA). Random assignment into groups will be computer generated, using 2 equal blocks (ratio 1:1).

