**Methods: Participants, interventions, and outcomes**

Study setting:

This trial will be conducted at the obstetrics and gynecology department of the university hospital Mongi Slim la Marsa, Tunis, Tunisia.

Study start date: February 8, 2021.

Participants’ eligibility criteria:

Inclusion criteria:

- Age ≥ 18 years old
- Full term (36 weeks and 3 days of gestation reached)
- Singleton gestation in cephalic presentation
- Bishop score of ≥ 6

Exclusion criteria:

- One or more previous caesarean scars (caesarean section, myomectomy with damage to the uterine cavity)
- Spontaneous rupture of membranes
- Spontaneous onset of labour
- Multiple pregnancies
- Malpresentation (breech, transverse or oblique presentations)
- Polyhydramnios
- Macrosomia (EFW ≥ 4000g)
- Narrow pelvic canal
- Severe foetal growth restriction (EFW ≤3^éme^ Percentile)
- Major foetal abnormalities
- Maternal infections: HIV infection, genital herpes, syphilis, hepatitis B or C
- COVID-19 infection
- Patient aged more than 40 years old
- Severe myopia
- Maternal cardiac disease
- Maternal fever
- Placenta previa
- Meconial amniotic liquid
- Patients declines to participate in the study

Interventions:

Each patient will receive comprehensive information regarding the study objective, and a reflection period will be allocated to facilitate the patient's informed decision-making process before granting their consent.

Prior to randomization, the investigator will conduct a double-check of patients' eligibility, and participants who meet the criteria will be sequentially assigned a study number.

Patients included in the study will be assigned to either early amniotomy (EA) or late amniotomy (LA) group:

In Group A (EA): Amniotomy will be performed soon after randomization, and oxytocin infusion will start 30 minutes later.

In Group B (LA): IOL will be initiated with oxytocin infusion, and amniotomy will be performed 4 hours later unless deemed necessary earlier (e.g. for non-reassuring fetal heart rate on the cardiotocography).

In case of impossibility of membrane rupture, the participant will be excluded.

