- Intrapartum and postpartum fever (Chorioamnionitis, endometritis…)
- Postpartum haemorrhage (PPH)
- Apgar scores at 1 and 5 min
- Neonatal sepsis and newborn admission to the neonatal intensive care unit (NICU).

Participant timeline:

Sample size:

The sample size was calculated using power calculations to detect a significant reduction in the time to APL. Based on the previous IOL performed in the department, the mean time needed to reach APL was 7± 3 hours and 36 minutes. Using an alpha error of 0.05 and 90 % power, aiming to decrease by 150 min the time to APL in EA group, a minimum of 44 patients are needed in each arm(15). The target is to enroll 100 women.

Recruitment:

The study will be presented to all medical provider to enhance the best adhesion to the protocol. To maximize patient recruitment, women will be sensitized and educated about the indications and potential benefits of the study. Rigorous monitoring of outcomes and maintaining high standards will be prioritized to attract more patients.

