**Methods : Assignment of interventions**

Allocation:

A random block allocation sequence will be used to generate with a 1:1 ratio using a computer-generated randomization program by an independent party, who will not be involved in enrolling participants or assigning them to interventions.

Blinding: This study will be a non-blinding study.

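### The open-label, one-department protocol describes its blocks in words that can mean blocks of two, and staff who knew this could foresee half the allocations

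*Protocol*

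**What the plan says.** The Introduction (Trial design) describes a non-blind trial with two parallel groups and then states: "Random assignment into groups will be computer generated, using 2 equal blocks (ratio 1:1".

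The Allocation paragraph, under Assignment of interventions, returns to the method: "A random block allocation sequence will be used to generate with a 1:1 ratio using a computer-generated randomization program by an independent party". That party is one "who will not be involved in enrolling participants or assigning them to interventions". No block length is given there, nor whether the length varies. The Blinding line adds: "This study will be a non-blinding study".

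Three other statements bear on the point:

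- Study setting: "This trial will be conducted at the obstetrics and gynecology department of the university hospital Mongi Slim la Marsa, Tunis, Tunisia".
- Interventions: "Prior to randomization, the investigator will conduct a double-check of patients' eligibility, and participants who meet the criteria will be sequentially assigned a study number".
- Sample size: "The target is to enroll 100 women".

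**The concern.** The sentence fixes a randomisation scheme in words that have at least three readings, and the readings differ greatly in how far ahead the list can be foreseen.

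The conditions for foreseeing it are present. The arms are openly different: one has its membranes ruptured shortly after randomisation, while the other starts with oxytocin and normally waits four hours. There is one department, so staff can plausibly know the last woman's arm. The block description is printed in the protocol, and the Recruitment paragraph says the study will be presented to all medical providers. Several entry criteria need clinical assessment, such as the Bishop score, estimated fetal weight and a narrow pelvis.

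A recruiter who knew the next arm could delay or decline a particular woman. The primary outcome is the time from starting oxytocin to 5 cm dilatation, so steering women with a more favourable cervix towards one arm would bias the main comparison. The planned ANCOVA can adjust only for factors that were recorded, not for a recruiter's unrecorded judgement.

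**Working it through.** **Inputs.** 100 women and a 1:1 ratio (protocol). Block length: 2 or 50, according to the reading, since two equal blocks of 100 women are 100/2 = 50 each. Assumption: the person enrolling knows the block length and the earlier allocations. The protocol gives no figure of its own for predictability.

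**Formulas**, for a permuted block of length 2m at 1:1:

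- Expected allocations known with certainty, per block: 2m/(m+1). As a share of all allocations this is 1/(m+1).
- Expected correct guesses per block, always naming the arm with more places left and tossing a coin at a tie: m + 0.5 × [2^(2m)/C(2m,m) − 1].

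**Blocks of two (m = 1).** Certain: 1/2, or 50 of 100. Correct guesses: 1 + 0.5 × (4/2 − 1) = 1.5 of 2, or 75%.

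**Two blocks of 50 (m = 25).** Certain: 1/26, or 3.8 of 100. Correct guesses: 57.9%.

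**Other lengths, for comparison:**

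| Fixed block length | Certain per 100 | Correct guesses |
|---|---|---|
| 2 | 50.0 | 75.0% |
| 4 | 33.3 | 70.8% |
| 6 | 25.0 | 68.3% |
| 8 | 20.0 | 66.6% |
| 50 | 3.8 | 57.9% |

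Simple randomisation would give 0 and 50%. A simulation of 100 allocations (5,000 runs) agreed: 50.0 and 75.1% for length 2, 33.3 and 70.9% for length 4, 3.8 and 57.9% for length 50.

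**Varying lengths.** Naming the under-represented arm does not require knowing the block size, because every completed block balances. For an equal mix of blocks of 4 and 6, the expected correct guesses are (2.833 + 4.1)/10 = 69.3%. Adding blocks of 8 (0.66607 × 8 = 5.329 correct per block) gives (2.833 + 4.1 + 5.329)/18 = 68.1%. Varying the size therefore lowers the guess rate only modestly. Its main gain is that someone who does not know the sizes can no longer be certain of the next arm.

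**Sample size.** This is not affected. With an SD of 216 min and a difference of 150 min, 2 × [216 × (1.960 + 1.282)/150]² = 43.6, which rounds up to the stated 44 per arm.

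**The case against.** The protocol does not say blocks of two. The sentence just before speaks of two parallel groups, so the phrase may be a loose way of saying two equal arms. Taken literally, it describes two blocks of 50, of which only about 4 allocations in 100 are certain. This stands: what is firmly established is an ambiguity, and the severe result belongs to one reading of it.

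The protocol also has safeguards. An independent party generates the list, and eligibility is checked before randomisation. This stands in part. Both protect the list and the order of events, but neither prevents the next arm being worked out from arms already seen, and no means of hiding the next assignment is described.

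A reader might infer that the Trial design and Allocation paragraphs prescribe different schemes. They do not. The second says "A random block allocation sequence will be used to generate with a 1:1 ratio", which is compatible with the first and merely less specific; a random block sequence need not have blocks of varying size. Leaving the block length out of the Allocation paragraph is not a fault either, since sizes are better kept from recruiters.

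A reader might also count the lack of stratification by parity as part of this problem. It is a separate design preference: chance imbalance is not selection bias, and the protocol gives no parity figures from which to size it.

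**Conclusion.** The point holds as a defect of wording with a potentially serious consequence. If blocks of two are meant, 50 of 100 allocations are certain in advance and 75% can be guessed. If two blocks of 50 are meant, the figures are about 4 and 58%. If only two equal arms are meant, the block length is unstated and no figure can be given.

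The larger figures rest on two assumptions that are plausible here but not stated in the protocol: that recruiting staff know the block length, and that they know the previous allocation. A reader might go further and infer that pairs were used, or that selection took place. The protocol shows neither; selection bias is a risk, not a finding. The matter should be settled because the damaging reading is a natural one, the trial is open, and a clear statement costs little.

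**What to change.** Replace the Trial design sentence with a single scheme that does not use blocks of two: computer-generated permuted blocks at 1:1, with randomly varying size. Include sizes larger than 4 and 6, because those two alone remain about 69% guessable, which is more than two blocks of 50. Keep the sizes in a document held by the independent party and out of the protocol given to recruiters. State that each allocation is revealed only after eligibility and the study number have been logged.

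The cost is a regenerated list and slightly less exact balance when recruitment stops within a block. If the largest block is 8, for example, the arms can differ by at most 4 women: 52 and 48 of 100, both above the stated minimum of 44 before any exclusions. No patients or staff are added.

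The protocol gives a start date in February 2021 and describes the analysis in the past tense, so the list may already have been used. In that case, report the block size actually used and, if it was two, disclose the predictability as a limitation of the trial.

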**Methods: Participants, interventions, and outcomes**

Study setting:

This trial will be conducted at the obstetrics and gynecology department of the university hospital Mongi Slim la Marsa, Tunis, Tunisia.

Study start date: February 8, 2021.

Participants’ eligibility criteria:

Inclusion criteria:

- Age ≥ 18 years old
- Full term (36 weeks and 3 days of gestation reached)
- Singleton gestation in cephalic presentation
- Bishop score of ≥ 6

Exclusion criteria:

- One or more previous caesarean scars (caesarean section, myomectomy with damage to the uterine cavity)
- Spontaneous rupture of membranes
- Spontaneous onset of labour
- Multiple pregnancies
- Malpresentation (breech, transverse or oblique presentations)
- Polyhydramnios
- Macrosomia (EFW ≥ 4000g)
- Narrow pelvic canal
- Severe foetal growth restriction (EFW ≤3^éme^ Percentile)
- Major foetal abnormalities
- Maternal infections: HIV infection, genital herpes, syphilis, hepatitis B or C
- COVID-19 infection
- Patient aged more than 40 years old
- Severe myopia
- Maternal cardiac disease
- Maternal fever
- Placenta previa
- Meconial amniotic liquid
- Patients declines to participate in the study

Interventions:

Each patient will receive comprehensive information regarding the study objective, and a reflection period will be allocated to facilitate the patient's informed decision-making process before granting their consent.

Prior to randomization, the investigator will conduct a double-check of patients' eligibility, and participants who meet the criteria will be sequentially assigned a study number.

Patients included in the study will be assigned to either early amniotomy (EA) or late amniotomy (LA) group:

In Group A (EA): Amniotomy will be performed soon after randomization, and oxytocin infusion will start 30 minutes later.

In Group B (LA): IOL will be initiated with oxytocin infusion, and amniotomy will be performed 4 hours later unless deemed necessary earlier (e.g. for non-reassuring fetal heart rate on the cardiotocography).

In case of impossibility of membrane rupture, the participant will be excluded.

The oxytocin administration protocol will be implemented utilizing a syringe infusion pump for optimal delivery. The initial dose will be set at rate of 2mUI/min, and it will be increased by and additional 2mUI every 30 minutes. To ensure safety, the infusion rate will not exceed 42 mUI per minute. In case of hyperstimulation or abnormalities in the cardiotocography (CTG) readings, the oxytocin infusion will be halted or reduced accordingly.

The progress of labor will be regularly monitored, with continuous monitoring of the cardiotocography (CTG), cervical dilatation, maternal temperature and blood pressure. All findings and observations will be documented in the patient's medical records.

Once regular and painful contractions have been established, epidural analgesia will be presented as a potential option for pain management.

The monitoring of labor relies on a one-to-one care. Cervical examinations will be performed every 4 hours in the absence of uterine contractions. However, if the patient experienced the onset of labor, the examinations will be conducted hourly, and the midwife documents the findings.

In cases where instrumental deliveries will be required, Simpson type forceps will be utilized. 5 IU of synthetic oxytocin will be administered intravenously at the delivery of the baby's anterior shoulder.

The decision to perform a cesarean section will be made by the supervising team in consultation with the attending consultant and after obtaining the patient's consent.

Concerning the newborn examination, the following parameters will be documented: gender, birth weight, Apgar score at 1, 5, and 10 minutes after birth, as well as signs of post-maturity.

Additionally, any neonatal resuscitation, complications, their reasons, and the duration of admission to the neonatology department will be recorded.

The Apgar score will be used to evaluate the newborn's well-being at birth. A score of seven or less will indicate neonatal distress, while a score of three or less will indicate a state of apparent death, necessitating immediate life-saving measures.

Postpartum examination, complications, and estimated blood loss throughout the entire process will be documented.

Outcomes:

The primary outcome is the duration between initiating the oxytocin infusion and the start of the active phase of labor (APL) defined as cervical dilatation of 5 cm(12,13)(14).

The secondary outcomes are:

- Time to vaginal delivery (VD)
- Caesarean delivery rate
- Intrapartum and postpartum fever (Chorioamnionitis, endometritis…)
- Postpartum haemorrhage (PPH)
- Apgar scores at 1 and 5 min
- Neonatal sepsis and newborn admission to the neonatal intensive care unit (NICU).

Participant timeline:

Sample size:

The sample size was calculated using power calculations to detect a significant reduction in the time to APL. Based on the previous IOL performed in the department, the mean time needed to reach APL was 7± 3 hours and 36 minutes. Using an alpha error of 0.05 and 90 % power, aiming to decrease by 150 min the time to APL in EA group, a minimum of 44 patients are needed in each arm(15). The target is to enroll 100 women.

Recruitment:

The study will be presented to all medical provider to enhance the best adhesion to the protocol. To maximize patient recruitment, women will be sensitized and educated about the indications and potential benefits of the study. Rigorous monitoring of outcomes and maintaining high standards will be prioritized to attract more patients.

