**Methods: Data collection, management, and analysis**

We aim to gather all the information’s about the patient base line characteristics, the details of the IOL progress and the maternal and fetal outcomes.

To ensure accuracy and efficiency, we will utilize pre-printed forms to record this information in the medical files (Patient data form). Subsequently, we will enter the recorded data into an Excel spreadsheet, facilitating easy management and analysis.

Quantitative variables with are expressed as mean ± standard deviation (SD), Medians [1st Q- 3rd Q]. Qualitative variables are expressed as percentages. The statistical analysis was carried out using “XLSTAT 2022.3.2.1346”. Data were analyzed using Student-test, Mann-Whitney and Chi square. To compare the two groups, per-protocol analysis was employed. Kaplan-Meier survival analysis with a log-rank test was utilized to compare the primary outcome measure. ANCOVA-test analysis was performed to identify independent factors that may influence the time to APL. All statistical tests were two sided and were performed at a significance level of α=0.05.

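### The 90% power at 44 per arm was calculated for a comparison of two means, while the primary outcome is tested by log-rank, for which no power was derived

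*Protocol*

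**What the plan says.** Protocol, Methods: Participants, interventions, and outcomes, Sample size. From earlier inductions in the department, "the mean time needed to reach APL was 7± 3 hours and 36 minutes". The calculation is described as "Using an alpha error of 0.05 and 90 % power, aiming to decrease by 150 min the time to APL in EA group", and the result is that "a minimum of 44 patients are needed in each arm". The recruitment target is 100 women, which is 50 per arm at the 1:1 ratio.

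Protocol, Methods: Data collection, management, and analysis. For the primary outcome, "Kaplan-Meier survival analysis with a log-rank test was utilized to compare the primary outcome measure". The same paragraph lists Student, Mann-Whitney and chi-square tests without tying any of them to an outcome, and an ANCOVA to look for factors that influence time to APL. It adds: "All statistical tests were two sided and were performed at a significance level of α=0.05".

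The protocol gives no hazard ratio, number of events, censoring rate, distributional form or separate SD for the early-amniotomy arm.

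**The concern.** A power statement belongs to a particular test. Here the inputs (a mean, an SD and a difference in minutes) are those of a comparison of means, but the test attached to the primary outcome is the log-rank test.

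The two do not have the same power in general. The log-rank test gives every event time the same weight and is most efficient when hazards are proportional. Lowering the mean from 420 to 270 min while holding the SD at 216 min raises the coefficient of variation from 216/420 = 0.51 to 216/270 = 0.80. In the skewed families one would normally use for a duration, that is not a proportional-hazards alternative, so some loss against the t-test is expected.

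At stake is whether the 90% can be relied on for the primary comparison. There is also a question of scale: the target is set in minutes, and a log-rank test by itself returns no difference in minutes.

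**Working it through.** **Inputs.** From the Sample size paragraph: control mean 7 h = 420 min; SD 3 h 36 min = 216 min = 3.6 h; target reduction 150 min = 2.5 h, so an early-amniotomy mean of 270 min = 4.5 h; alpha 0.05; power 90%; 44 per arm, with 50 per arm as the target. Two-sided testing comes from the analysis section.

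**Step 1: reproduce the plan's figure.** For two means with a common SD,

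n per arm = 2(z₀.₉₇₅ + z₀.₉₀)²(SD/difference)² = 2(1.960 + 1.282)²(216/150)² = 2 × 10.51 × 2.0736 = 43.6, so 44.

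This matches exactly. The normal approximation gives 90.3% power at 44. The exact t-test gives 89.6% at 44 and 93.0% at 50. A one-sided alpha would give 36 per arm and 80% power would give 33, so neither explains the figure. The 44 is therefore a two-means calculation that takes SD 216 min in both arms.

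**Step 2: power of the log-rank test under the same common SD.** Simulated trials with means 7 h and 4.5 h, SD 3.6 h in both arms, no censoring, two-sided 5% level. Distributions are matched on mean and SD, or the control distribution is shifted down by 2.5 h. There were 5,000 trials per cell (8,000 for the shift) and 1,500 for the t-test. The log-rank rejection rate under no difference was 5.6%, so the test was not conservative.

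| Shape | Log-rank, 44 | Log-rank (shift), 44 | t-test, 44 | Log-rank, 50 | Log-rank (shift), 50 | t-test, 50 |
|---|---|---|---|---|---|---|
| Normal | 85% | 84% | 91% | 88% | 88% | 91% |
| Gamma | 79% | 77% | 89% | 83% | 81% | 93% |
| Lognormal | 85% | 79% | 87% | 90% | 83% | 91% |
| Weibull | 77% | 77% | 89% | 82% | 82% | 93% |

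A separate set of 2,000 trials per cell gave 76% (Weibull), 80% (gamma) and 88% (lognormal) at 44 per arm. Across all runs the range is about 76-88% at 44 and 81-90% at 50. The 88% comes from that shorter set; longer runs put the lognormal at 85-86%.

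**Step 3: how much depends on the early-amniotomy SD.** Log-rank power at 44 per arm, 4,000 trials per cell. The last column is the SD that keeps the coefficient of variation constant, 3.6 × 4.5/7 = 2.31 h.

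| Shape | SD 3.6 h | 3.3 h | 3.0 h | 2.7 h | 2.31 h |
|---|---|---|---|---|---|
| Normal | 83% | 91% | 96% | 98% | 99% or more |
| Gamma | 78% | 84% | 89% | 93% | 97% |
| Lognormal | 86% | 89% | 91% | 94% | 97% |
| Weibull | 76% | 83% | 89% | 94% | 98% |

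Power reaches about 90% at an SD of roughly 3.3 h for the normal and lognormal and roughly 3.0 h for the gamma and Weibull.

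**Step 4: other sensitivities, common SD.** Reaching 90% log-rank power takes about 50-64 per arm, depending on shape. With 10-20% random censoring (an assumption; the protocol gives no rate), power at 44 per arm is about 71-82%. Rounding times up to hourly examinations leaves it at about 79-87%.

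**The case against.** The strongest reply is that the documents do not fix the log-rank power at all. They give one mean, one SD from past inductions and one target reduction. A range of 76-88% needs a chosen distribution and the same SD in an arm whose mean has fallen by more than a third. For a positive duration it is plausible that the spread falls with the mean, and then log-rank power at 44 per arm is 97% or more. That stands, and it rules out the flat statement that the trial is underpowered on its own figures. What remains is that the common SD is the assumption that yields the plan's 44, and under it the named test does not deliver 90% at 44 per arm.

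Second, the target is 100 women, not 88. This also stands: at 50 per arm the gap to 90% is about 0-9 points. The per-protocol analysis may remove some of that margin, but no exclusion rate is given.

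Third, the log-rank test is a legitimate choice for a time outcome that can be censored, and the choice of an effect measure with a CI is commonly left to a statistical analysis plan. Both are fair. The point is not the choice of test, but that this protocol states a power and a test that do not belong together.

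Two stronger readings are tempting and not supported. A reader might infer that the primary result cannot be compared with the 150-min target. The analysis section provides means with SDs, medians with quartiles and an ANCOVA on time to APL, so a difference in minutes is obtainable; it is just not named as the primary effect. A reader might also infer, because in the late arm "amniotomy will be performed 4 hours later", that the hazards must converge and the log-rank test loses heavily. The protocol allows that amniotomy earlier and nowhere says the hazards become equal afterwards. Putting a number on the loss would require an effect size it does not contain.

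**Conclusion.** The mismatch is real and its size is modest. The arithmetic behind 44 per arm is correct, but for a comparison of means. For the log-rank test named as the primary comparison no power was derived. With SD 3.6 h in both arms and all women reaching APL, that test falls about 2-14 points short of 90% at 44 per arm (76-88%) and about 0-9 points short at 50 per arm (81-90%). The result depends on equal SDs and on the distribution, neither of which the protocol states. A smaller early-amniotomy SD removes or reverses the shortfall, and censoring would deepen it. So the documents support saying that the 90% has not been shown for the primary test, not that the trial is underpowered.

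**What to change.** Choose one of two routes in the Sample size and analysis paragraphs.

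1. Keep the log-rank test as primary and restate its power, giving the SD assumed in each arm, the distribution and the censoring assumed. With a common SD and no censoring, that is about 76-88% at 44 and 81-90% at 50 per arm. If a smaller early-amniotomy SD is assumed, give its basis.
2. Name the comparison of means, for which the 44 was calculated, as the primary test and keep the log-rank test as supportive. If some women may not reach APL, use a restricted mean with a time horizon fixed in advance.

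Under either route, report the difference in mean (or restricted mean) time to APL in minutes with a 95% CI beside the test, so that the result can be set directly against the 150-min target. Because the analysis section is written in the past tense, the first route is the safer one if outcomes by arm have already been seen.

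The cost is wording, a time horizon if the restricted mean is used, and a stated power that may be slightly less favourable. Neither route needs more patients.
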